#### Methods in analysis to handle protocol non-adherence and any statistical methods to handle missing data {20c}

In the primary analysis, multiple imputation will be used if more than 5% of the data are missing. Imputation will be done separately within each intervention group, utilising predictive mean matching based on the nearest three neighbouring values. The imputation model will incorporate all variables from the dataset except censored variables and variables derived from original data, such as body mass index (calculated from height and length) and transferrin saturation (to be derived from serum concentrations of iron and UIBC). We will employ a process involving at least 20 imputations, to be conducted iteratively through chained equations. Additionally, a per-protocol analysis will be performed to determine the sensitivity of the intention-to-treat analysis. The per-protocol analysis will be a comparison of the treatment groups that include only those patients who completed the treatment originally allocated and have endpoint measurement.

#### Methods for additional analyses (e.g. subgroup analyses) {20b}

We will use multiple fractional polynomial regression analysis to explore to what extent group differences in haemoglobin concentration depend on iron status at baseline (as indicated by serum ferritin concentration) and on inflammation at baseline (as indicated by serum concentrations of CRP and AGP). When there is statistical support for such effect size modification, we will report intervention effects with 95% CIs.

Adverse events will be analysed per protocol analysis. The number of adverse events and type of adverse event by treatment group will be reported as detailed in Table 4. If the number of reported adverse events is less than 20 per adverse event type per intervention group, no formal statistical procedure will be conducted. For adverse effects that occur relatively frequently (more than 20 per intervention arm), we will evaluate the group differences in the incidence of adverse events using Poisson or negative binomial regression models with zero inflation as appropriate.

**Table 4 Tab4:** Number of adverse events by treatment type (per-protocol analysis)

Diagnosis	Haem iron	Ferrous Sulphate
**Respiratory**	–	–
Upper respiratory tract infection	–	–
Pneumonia	–	–
Bronchiolitis	–	–
**Gastrointestinal**	–	–
Gastroenteritis	–	–
Acute watery diarrhoea	–	–
Persistent diarrhoea	–	–
Bacillary dysentery	–	–
**Skin**	–	–
Skin infection	–	–
Abscess	–	–
Conjunctivitis	–	–
Total number of AE	–	–

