### Adverse event assessment and reporting {11b}

All adverse events and serious adverse events will be recorded by the research clinician or nurses in RedCap and treatment/referral provided where required. Bi-weekly meetings with the field team will be held and a summary of field activities including the number of participants who consented, screened and any adverse events reported. Field workers will immediately call the research clinician/study nurse if they find a participant is unwell and will seek advice if the investigational product should be withheld. Reported fever will be confirmed by measuring the axillary temperature using a digital thermometer in the field by field workers. The outcome will be reported to the clinical team immediately who will decide on treatment/clinical referral where required. All symptoms or signs reported or observed will be documented after evaluation by the study nurse or clinician.

Investigational products shall be withheld for 7 days following the detection of the following conditions: (1) confirmed fever (axillary temperature > 37.5 °C) not associated with teething or vaccination, (2) visually confirmed bloody diarrhoea, (3) hospitalisation for somatic illness and (4) treatment with antibiotics for any confirmed or suspected infection.

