### Outcome measures {12}

The primary and secondary outcomes will be collected at baseline (day 0) and endline (day 84) at the study sites. The *primary endpoints* are haemoglobin concentration and serum ferritin concentration at day 84. Secondary endpoints related to the primary objective will include proportion of children with anaemia (haemoglobin concentration < 11.0 g/dL) [12] at study day 84, proportion of children with iron deficiency (ID) (ferritin < 12 μg/L or < 30 μg/L in the presence of inflammation) [13] and proportion of children with iron deficiency anaemia (IDA) (haemoglobin concentration < 11.0g/dL and sTfR mg/L/logFerritin ratio > 2.0, ferritin < 30 μg/L in the presence of inflammation (CRP > 5 mg/L)) [14] at day 84. We will also determine other haematology (MCV, MCH, MCHC, reticulocyte-haemoglobin concentration and reticulocyte count) and iron status markers (iron, transferrin, soluble transferrin receptor, hepcidin, erythropoietin, erythroferrone, transferrin saturation, unbound iron binding capacity) at day 84. We will also measure the effect of the intervention on growth.

Safety measures will consist of the incidence of adverse events and serious adverse events per child over the observation period and serum concentrations of inflammatory markers (C-reactive protein/α1-acid glycoprotein) at day 84 and faecal calprotectin.

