The primary analysis concerns the effects of the intervention on haemoglobin concentration and serum ferritin concentration at day 84 after the start of the intervention (day 0), adjusting for the same variable measured at baseline. The analysis will be based on a modified intention-to-treat approach, including all randomised children who received at least one supplemental dose. Effect sizes will be reported with 95% CIs as detailed in Table 3.

**Table 3 Tab3:** Effect of iron supplementation on primary and secondary outcomes (intention-to-treat population)

Outcome variable	Haem iron	Ferrous sulphate	Group difference, unadjusted (95% CI)	*p*-value	Group difference, adjusted (95% CI)	*p*-value
Serum iron, μmol/L	–	–	–	–	–	–
Serum ferritin, μg/L	–	–	–	–	–	–
Serum soluble transferrin receptor, mg/L	–	–	–	–	–	–
Serum transferrin, g/L	–	–	–	–	–	–
UIBC, μmol/L	–	–	–	–	–	–
TSAT	–	–	–	–	–	–
Serum sTfR/log_10_(ferritin) index	–	–	–	–	–	–
Haemoglobin, g/dL	–	–	–	–	–	–
Anaemia (haemoglobin < 11.0 g/dL)	–	–	–	–	–	–
MCV, fL	–	–	–	–	–	–
MCH, pg	–	–	–	–	–	–
MCHC, g/dL	–	–	–	–	–	–
Reticulocyte count, × 10^9^/L	–	–	–	–	–	–
Reticulocyte count, %	–	–	–	–	–	–
Immature reticulocyte fraction, %	–	–	–	–	–	–
Reticulocyte haemoglobin, pg	–	–	–	–	–	–
Serum hepcidin, μg/L	–	–	–	–	–	–
Serum erythropoietin, IU/L	–	–	–	–	–	–
Serum erythroferrone, μg/L	–	–	–	–	–	–
Serum C-reactive protein, mg/L	–	–	–	–	–	–
Serum *α*_1_-acid glycoprotein, g/L	–	–	–	–	–	–
Height-for-age *z*-score, SD	–	–	–	–	–	–
Weight-for-age *z*-score, SD	–	–	–	–	–	–
Height-for-weight *z*-score, SD	–	–	–	–	–	–

In secondary analyses, we will adjust intervention effects for sex, age, haemoglobin concentration and serum concentrations of ferritin and soluble transferrin receptor at baseline (continuous variables except sex). Fractional polynomial regression analysis will be utilised to explore the relationship between the magnitude of the intervention effect on haemoglobin levels and the baseline iron status.

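### Adverse events are compared between arms only in the per-protocol set, so events in children who stop, withdraw, die or miss day 84 are left out of that comparison

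*Protocol article*

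**What the plan says.** All places are in the protocol article.

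- *Methods for additional analyses {20b}*: "Adverse events will be analysed per protocol analysis". The title of Table 4, the adverse-event table, names the same set. No other set is named for adverse events.
- *Methods in analysis to handle protocol non-adherence {20c}*: the per-protocol comparison will "include only those patients who completed the treatment originally allocated and have endpoint measurement". Its stated purpose is different: "a per-protocol analysis will be performed to determine the sensitivity of the intention-to-treat analysis".
- *Statistical analysis {20a}*: the primary efficacy analysis uses a modified intention-to-treat set, "including all randomised children who received at least one supplemental dose".
- *Outcome measures {12}*: "Safety measures will consist of the incidence of adverse events and serious adverse events per child over the observation period", together with inflammatory markers.
- *Adverse event assessment and reporting {11b}*: "Investigational products shall be withheld for 7 days following the detection of the following conditions". The list covers confirmed fever, bloody diarrhoea, hospitalisation and antibiotic treatment.

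**The concern.** Membership of the per-protocol set is decided after randomisation, by completing treatment and reaching the endpoint. An adverse event can cause a child to fail either condition. When it does, all of that child's events are removed from the comparison, including the one that ended participation. The harms most likely to be lost are those serious enough to end treatment or follow-up.

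The Discussion links possible policy change to haem iron proving both efficacious and safe. A between-arm comparison confined to completers is weak support for the safety half of that claim in infants.

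**Working it through.** No stated figure decides this point. The check sets the definitions side by side and then illustrates the size.

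**1. Who is counted.**

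- Completes treatment and has the endpoint: in the per-protocol set and in the at-least-one-dose set.
- Stops the supplement but attends day 84: not per-protocol; in the at-least-one-dose set.
- Withdraws, or misses day 84: not per-protocol; in the at-least-one-dose set if dosed.
- Dies before day 84: the definition does not mention death, but there can be no day-84 measurement, so not per-protocol; in the at-least-one-dose set if dosed.
- Has product withheld for 7 days and resumes: depends on what completing treatment means, which the article does not settle.

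Only the at-least-one-dose set fits a measure defined per child over the observation period.

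**2. How many children.** Randomised 208 and dropout 5% (*Sample size determination {14}*): 0.05 × 208 = 10.4, about 10 children. Those who stop the supplement but still attend day 84 may come on top, because the article does not say what dropout covers.

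**3. What selection can do.** The event risks and leaving rates here are assumptions; the documents give none. There are 208 / 2 = 104 children per arm. With true risk p and a share q of affected children leaving the set (and no unaffected child leaving), the per-protocol risk is

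104p(1 − q) / (104 − 104pq).

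The cases are kept within the 10.4 children of planned dropout.

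- (a) Risks 10% v 20%, q = 25% in both arms. Counts fall from 10.4 v 20.8 to 7.8 v 15.6; denominators are 101.4 and 98.8; risks are 7.7% v 15.8%. The difference shrinks from 10.0 to 8.1 points, while the ratio hardly moves (2.0 to 2.05). Children removed: 2.6 + 5.2 = 7.8.
- (b) Equal risks of 10%, q = 10% v 50%. Counts 9.36 v 5.2; denominators 102.96 and 98.8; risks 9.1% v 5.3%; ratio 0.58 where the truth is 1. The arm that loses more ill children looks safer. Children removed: 1.04 + 5.2 = 6.24.
- (c) Risks 10% v 20%, q = 0 v 50%. Risks become 10.4/104 = 10.0% v 10.4/93.6 = 11.1%; ratio 1.11 where the truth is 2. Children removed: 10.4. This is an extreme case, with the whole planned dropout made up of affected children in one arm.

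Case (a) understates incidence, case (b) creates a difference and case (c) nearly removes one.

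**4. Side effect on testing.** Section {20b} runs no formal procedure when an event type has fewer than 20 events per group. In case (a), at one event per affected child, the higher arm falls from 20.8 to 15.6 and crosses that threshold because of the choice of set alone.

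**The case against.** The strongest reply is that harms in non-completers do not go unseen. All adverse events are captured whether or not related, an event associated with discontinuation will be described, and the DSMB reviews safety data. CRP and AGP, which are named safety measures, are compared in Table 3 under intention-to-treat. Planned dropout is small, and the primary endpoints are untouched. All of this stands. But none of it returns a non-completer to the between-arm comparison of adverse events, which is the part at issue.

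A second reply is that withholding product for 7 days is itself a protocol rule, so a child who resumes is following the protocol and may well count as having completed. That also stands. A reader might infer from the withholding rule that every child with a fever or an antibiotic course leaves the safety table. The article does not support this: it speaks of completing the allocated treatment, not of taking all 84 doses, and it gives no illness rate from which to estimate the share affected. What remains is that completion is left open, and the selection problem would be larger under the stricter reading.

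**Conclusion.** The point holds as a stated choice that is wrong as written. The article assigns adverse events to a completers-only set, and this conflicts with its own per-child safety measure. About 10 of 208 children are involved at planned dropout. The true number depends on actual non-completion and on how completion is defined, and neither is shown. The illustrated distortions rest on assumed risks and leaving rates; they show what is possible, not what is expected.

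Three stronger readings are not supported:

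- A reader might infer that the comparison misses the harms it is meant to detect. It does not miss them all, because respiratory, gastrointestinal and skin events in completers are counted.
- A reader might infer that the bias always runs toward no difference. Case (b) shows the opposite.
- A reader might take the absence of a serious-adverse-event row in Table 4 as a further error. Table 4 is a shell by diagnosis in a condensed article, serious events are recorded and named as a safety measure, and such detail is commonly left to the full protocol or analysis plan.

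**What to change.** Replace the sentence in {20b} and the title of Table 4 so that adverse and serious adverse events are analysed in all randomised children who received at least one dose, the set already defined in {20a}. Count events over all observed time, including the 2 weeks of post-supplementation monitoring, and enter observed time as the offset in the planned Poisson or negative binomial models, so that children who leave early contribute what was observed. A per-protocol table may stay as a supplement; if it does, state whether children whose product was withheld under {11b} count as having completed treatment.

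The cost is a change of wording and one re-run table. No new data are needed, since events are already recorded irrespective of relatedness.

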## Methods/design {8}

### Study design

This will be a 2-arm parallel randomised controlled superiority trial, with participants, field staff outcome assessors and biostatisticians blinded to the treatment arm. The trial will be conducted in rural Gambia, and potential participants will be recruited from vaccination clinics or their communities. A total of 208 participants will be randomised to either haem iron or ferrous sulphate using a 1:1 allocation ratio and supplemented daily for 84 days (Fig. 2).

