### Statistical plan

#### Sample size determination {14}

The sample size was determined by the primary endpoints, haemoglobin concentration and serum ferritin concentration, which will both be measured 84 days after randomisation (Fig. 2) using Microsoft Excel™ with a 5% dropout rate; a total of 208 children will be randomised, which will be sufficient to (a) provide 90% probability that, if the real group difference in haemoglobin concentration is 5.0 g/L or more, the 95% CI for the difference would exclude 0 [calculation based on the assumption that the SD for haemoglobin is 10g/L for each group (estimate based on previous experience in many previous trials in African children)] and (b) have 90% probability that, if the real change of the geometric mean serum ferritin concentration in the haem group iron relative to the control group is 75% or more, the 95% CI for the ratio would exclude 0 [calculation based on the additional assumption that the variance of log_e_-(serum ferritin concentration, μg/L) equals 1.232 for each group [15]].

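### Whether an adverse-event type is formally compared depends on each arm's own event count, and the rule is undefined at exactly 20 and when the arms fall on opposite sides of 20

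*Protocol article*

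**What the plan says.** The rule is in the protocol article, Methods for additional analyses {20b}. Two sentences set it:

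- The first bars formal comparison of a type whose count is low: "less than 20 per adverse event type per intervention group, no formal statistical procedure will be conducted".
- The second plans a comparison of incidence between the groups "using Poisson or negative binomial regression models with zero inflation as appropriate". It limits this to the more common types, with the words "For adverse effects that occur relatively frequently (more than 20 per intervention arm").

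The same section provides for counts whatever their size: "The number of adverse events and type of adverse event by treatment group will be reported as detailed in Table 4". Table 4 has ten diagnoses under three system groups, plus a total. It has one column per arm and no column for a rate, an effect estimate or an interval.

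Outcome measures {12} lists as a safety measure the "incidence of adverse events and serious adverse events per child over the observation period". Study design gives the size of the trial: "A total of 208 participants will be randomised to either haem iron or ferrous sulphate using a 1:1 allocation ratio". Supplementation lasts 84 days.

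**The concern.** A threshold that decides whether a comparison is made should not depend on the comparison itself. Here it is applied to each intervention group separately, so two event types with the same total can be treated differently only because their events are split differently between the arms.

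The two sentences also leave gaps. One says fewer than 20 and the other more than 20, so a count of exactly 20 falls under neither. Neither says what happens when one arm is below 20 and the other above. That choice would then be made once the counts by arm are known, which a pre-specified rule is meant to prevent.

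At stake is a stated safety outcome. An event type on the wrong side of the rule gets two counts in Table 4 and no measure of how far the arms differ or how uncertain that difference is.

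**Working it through.** **Inputs.** From the article: the threshold of 20 per arm, and 208 children allocated 1:1, which is 208 / 2 = 104 per arm. The article gives no derivation of the threshold, so there is no planned figure to reproduce. It gives no expected event rates, so every count pair below is an illustration. Two-sided 0.05 is assumed for adverse events; the article implies it only for the primary endpoints, where "the 95% CI for the difference would exclude 0".

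**Method.** With equal exposure and independent Poisson events, the count *a* in one arm, given the total *a + b*, is Binomial(*a + b*, 0.5) if the rates are equal. The exact two-sided p-value follows. If (L, U) is the exact 95% interval for the share *a*/(*a + b*), the rate ratio *a/b* has the interval L/(1 − L) to U/(1 − U). For 19 v 2, the share 19/21 has interval 0.696 to 0.988, which gives a ratio of 19/2 = 9.5 with interval 2.3 to 84.

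**Two readings.** A: both arms must exceed 20 (more natural, given the per-group and per-arm wording). B: one arm above 20 is enough.

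| Split | Rate ratio (exact 95% CI) | Exact p | Compared under A? | Compared under B? |
|---|---|---|---|---|
| 45 v 10 | 4.5 (2.2 to 10.0) | 0.000002 | no | yes |
| 40 v 15 | 2.7 (1.4 to 5.2) | 0.001 | no | yes |
| 19 v 2 | 9.5 (2.3 to 84) | 0.0002 | no | no |
| 19 v 4 | 4.75 (1.6 to 19) | 0.003 | no | no |
| 22 v 21 | 1.05 (0.55 to 2.0) | 1.0 | yes | yes |

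**Smallest detectable split under A.** Both counts must be at least 21. 21 v 36 gives p = 0.063 and 21 v 37 gives p = 0.048. So 21 + 37 = 58 is the smallest total that can pass the rule and reach p < 0.05.

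**How often the rule admits a comparison.** The true expected counts are assumed, and the probabilities are exact Poisson.

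| Expected counts | Power, no threshold | A: comparison allowed | A: allowed and p < 0.05 | B: allowed and p < 0.05 |
|---|---|---|---|---|
| 5 v 15 | 54% | 0% | 0% | 8% |
| 5 v 20 | 83% | 0% | 0% | 43% |
| 15 v 45 | 97% | 8% | 7% | 97% |
| 20 v 40 | 70% | 44% | 21% | 70% |
| 30 v 60 | 87% | 97% | 84% | 87% |

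Under A the loss is greatest when one arm's count is low. Under B it is confined to types where both arms are small.

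**Sensitivity to repeated events in the same child.** Take z = (*a* − *b*)/√(*a + b*) and divide by √φ, where φ is an assumed variance inflation. For 19 v 4, z = 15/√23 = 3.13; φ = 2 gives p = 0.027 and φ = 3 gives 0.07. For 40 v 15, z = 25/√55 = 3.37; the values are 0.017 and 0.05. For 45 v 10 and 19 v 2, p stays below 0.05 at φ = 3 (0.006 and 0.03). The exact p-values above are therefore too small if events cluster within children, but the rule's dependence on the split does not change.

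**The case against.** A reader might infer that the rule leaves the most unbalanced events untested and so biases the safety conclusion towards no difference. The article does not support this as a general statement, for four reasons.

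- **The reading is unsettled.** 45 v 10 and 40 v 15 go uncompared only if both arms must exceed 20. The first sentence can also be taken to bar comparison only when each arm is below 20, and then large imbalances are tested.
- **No test is not a finding of no difference.** The article states no such inference. Table 4 shows every count by diagnosis and arm, and the data safety monitoring board reviews safety data (section {21a}). A 19 v 2 split would be seen.
- **Describing sparse events without tests is common practice.** With 104 children per arm there is little power for truly rare diagnoses. Table 4 has 10 + 3 + 1 = 14 rows. If all were tested at 0.05 and were independent, the chance of at least one false positive would be 1 − 0.95^14 = 51%. Restraint is defensible.
- **A journal article condenses the plan.** A fallback method for small counts may properly sit in an analysis plan that is not shown, so its absence is not the point here.

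These objections stand against the broader inference. They do not remove the narrower point. The article states its rule in terms of arm-specific counts, which ties eligibility to the result under either reading. The two sentences do not cover exactly 20 or opposite-side counts. Under either reading 19 v 2 gets no formal comparison, and Table 4 offers no estimate or interval in its place.

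**Conclusion.** The point holds in its narrower form. The rule makes formal comparison depend on how events split between the arms, and it is undefined at exactly 20 and when the arms lie on opposite sides of 20.

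The size depends on the reading. If both arms must exceed 20, a type needs at least 58 events in total before it can both pass the rule and reach p < 0.05, and splits such as 45 v 10 are not compared. If one arm is enough, the loss is limited to types with at most 20 events in each arm, such as 19 v 2.

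The loss is of effect estimates and intervals, not of reporting. The figures rest on assumed counts, equal exposure, independent events and a two-sided 0.05 level. The primary endpoints are not affected. This is an inexpensive improvement to the safety analysis that should be made.

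**What to change.** 1. Replace the per-arm threshold with one on the pooled count of each event type over both arms, read while still blinded. Use it only to decide when Poisson or negative binomial regression is fitted, and state on which side the boundary value falls.
2. For every row of Table 4, including types below the threshold, report the number of children with at least one event and a rate ratio or risk difference with a 95% CI. Use exact intervals for sparse types, and allow for repeated events in the same child where they occur.
3. Label these estimates descriptive, and make no multiplicity-adjusted claims from them.

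No new data are needed. The cost is a few more columns in Table 4 and wide intervals for rare events.
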